### 1.6 OUTCOME (O)

#### 1.6.1 Primary

- 1) (Cost-)effectiveness of structured survivorship care at the BETER clinics in terms of:
  - a. Burden of disease in disability adjusted life years (DALYs) from CVD (including risk factors for CVD), breast cancer, hypothyroidism and functional asplenia
  - b. Health care costs related to CVD (including risk factors for CVD), breast cancer, hypothyroidism and functional asplenia
  - c. Health-related quality of life (HRQoL) and QALY's using the 36-item Short Form Health Survey (SF-36) and the 5 dimension/5-level EuroQoL (EQ-5D-5L) questionnaire
  - d. Health-related productivity losses using the iMTA Productivity Cost Questionnaire (iPCQ).
- 2) The yield of previously undiagnosed adverse events from screening and the incidence of adverse events during follow-up
  - a. At prevalent and incident screening of survivors attending the BETER clinic (for those survivors in the intervention group who are attending the BETER clinic)
  - b. From hospital records, Netherlands Cancer Registry, The National Heart Registry, GP records, Dutch Hospital Data registry, and BETER questionnaire: for all included survivors, to allow valid comparison between the intervention and comparison groups

#### 1.6.2 Secondary

- 1) Adherence to the BETER guidelines by
  - a. HL survivors
  - b. health care providers
- 2) (Non-)attendance at the BETER clinics
- 3) Health care use in both groups, incl. screening practices in survivors who do not attend the BETER clinic between 2013-2016 and 2021-2024
- 4) Knowledge about late adverse effects and risk perception of late effects of lymphoma treatment
- 5) Distress about late effects of lymphoma treatment

##### 1.6.1.1. Assessment of Yield of Screening and Incidence of Adverse Events

For the primary outcomes, we will first determine the yield of previously undiagnosed adverse events during follow-up, i.e. between 2013-2016 and 2021-2024. This information will be extracted from hospital medical records, the survivors' general practitioners, disease registries and the self-administered BETER questionnaire.

Before their clinic visit survivors are asked to complete a questionnaire on their current health, medical history, and lifestyle. This so-called BETER questionnaire helps healthcare providers to focus on actual symptoms of late effects and on lifestyle during the consultation. The questionnaire contains items on general background (e.g. marital status, level of education), medical history (adverse events, including reproductive history and fatigue), family history, medication, screening history, physical activity, weight, alcohol, smoking and recreational drug use, as well as psychosocial problems, difficulties with employment, insurance coverage, and mortgages. The BETER questionnaire will also be mailed to eligible survivors who decided not to visit a BETER clinic. In line with the intervention group, the survivors in the control group will fill in the BETER questionnaire at their first BETER visit in 2021-2024 or through mail (for non-responders). The BETER questionnaire thus provides the proposed project with important information on existing morbidity/diseases prior to the first BETER visit and on characteristics of the BETER visitors. The response to The BETER questionnaire is very high, ranging between 90-95%.

For the intervention group trained data managers will access the BETER medical records in the BETER clinics and collect the relevant data from all BETER visits, including all screening/diagnostic tests during follow-up and their results. For all survivors included in the study (intervention and comparison groups) we will obtain information on the incidence of clinical events of interest through linkage with disease registries. Information on second malignancies will be obtained from The Netherlands Cancer Registry, information on cardiac interventions will be obtained from The National Heart Registry, information on hospital admissions for CVD and serious infections (overwhelming post-splenectomy infections) will be obtained from Dutch Hospital Data and cause of death for those who died during follow-up will be obtained from Statistics Netherlands. We will also approach the general practitioners of all patients to obtain data on CVDs (especially those not requiring hospital admission, such as angina pectoris), cardiovascular risk factors (hypertension and hypercholesterolemia) and hypothyroidism.

Survivors' informed consent for the above data collection is asked at the first visit to a BETER clinic. For included survivors who choose not to visit a BETER clinic informed consent for linkage with disease registries and approach of general practitioner is requested by mail. Currently over 97% of all patients visiting a BETER clinic has provided consent. Informed consent for the control group will be obtained during the patients' first visit at a BETER clinic in 2021-2024 and is not necessary for deceased individuals.

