### 1.5 FOLLOW-TIME (T)

To facilitate follow-up of at least 5 years at the BETER clinics, the follow-up of lymphoma survivors in the intervention group starts in 2013-2016, when they were first invited to attend the BETER clinic, and ends in 2021-2024 at their most recent BETER visit. The start of follow-up of survivors in the control group will correspond to that of the intervention group and ends at their first BETER visit in 2021-2024. The follow-up of survivors who do not attend the BETER clinic (i.e. non-attenders in both the intervention and control groups) ends on completion of the mailed questionnaires. Furthermore, if survivors either in the intervention group or comparison group die during follow-up, follow-up ends at death. Expected median follow-up time is 8 years.

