#### 1.6.2.3. Health Care Use, incl. Screening Practices

Information on the overall health care use (medication, GP visits, hospital visits and hospitalisation) between 2013-2016 and 2021-2024 in the intervention and control groups will be extracted from hospital medical records, the survivors' general practitioners, disease registries and the self-administered BETER questionnaire. It will allow us to compare overall health care use between the intervention and control groups, as well as compare survivors who have accepted and declined to attend the BETER clinic. This will provide more insight into the patient characteristics of those who declined to attend the BETER clinic: e.g. are they not experiencing any health complaints or is their health compromised and are they treated/screened for late treatment effects elsewhere? See also 1.6.2.2.

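### The BETER questionnaire is used to compare the arms, but it falls near the start of follow-up for intervention attenders and at the end for controls

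*Protocol*

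**What the plan says.** **Role of the form.** Section 1.6.1, primary outcome 2b, lists it last among the sources of incident adverse events: "BETER questionnaire: for all included survivors, to allow valid comparison between the intervention and comparison groups". Section 1.6.1.1 sets the target as "the yield of previously undiagnosed adverse events during follow-up, i.e. between 2013-2016 and 2021-2024" and again names the questionnaire as a source. Section 1.6.2.3 draws overall health care use over the same period from hospital and general practitioner records, "disease registries and the self-administered BETER questionnaire", and compares it between the arms and between those who accepted and those who declined the clinic.

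**When it is completed.** Section 1.6.1.1: "Before their clinic visit survivors are asked to complete a questionnaire on their current health, medical history, and lifestyle". For the other arm, and expressly in parallel with the intervention group, "the survivors in the control group will fill in the BETER questionnaire at their first BETER visit in 2021-2024". The same section says that the form supplies "information on existing morbidity/diseases prior to the first BETER visit". Survivors who do not visit a clinic get it by mail.

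**Follow-up.** Under section 1.5, follow-up of the intervention group runs from first invitation in 2013-2016 to the most recent visit in 2021-2024. Controls start at the corresponding date and stop at their first visit in 2021-2024. For non-attenders in both arms, follow-up "ends on completion of the mailed questionnaires".

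**Contrast.** Sections 1.6.1.4 and 1.6.1.5 place the SF-36, EQ-5D-5L and iPCQ at the end of follow-up. Section 8.3.1 confirms a single measurement of quality of life and productivity losses at that point in all survivors. The BETER questionnaire is not listed with them.

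**The concern.** The two arms are matched on the visit at which the form is completed, not on the period that it describes. A form completed before a first visit in 2013-2016 cannot report what happened between then and 2021-2024. The same form completed in 2021-2024 can. Using both as one source for that window means that self-report is ascertained differently in the two arms.

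At stake are the yield and incidence comparison in primary outcome 2b and the secondary comparison of health care use. The most exposed items are those that rest on the survivor's own account: milder morbidity, medication, and screening or care received elsewhere.

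The comparison of attenders with non-attenders has a related weakness. If non-attenders' forms date from the end of follow-up, illness that arose after the decision not to attend could be taken for a reason behind it.

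**Working it through.** **Step 1. Set the timing side by side** (sections 1.1, 1.5 and 1.6.1.1).

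| Group | Follow-up starts | Follow-up ends | Form completed | Follow-up covered by the form |
|---|---|---|---|---|
| Intervention attenders | Invitation, 2013-2016 | Most recent visit, 2021-2024 | Before first visit | Almost none (only the gap from invitation to first visit) |
| Control attenders | Corresponding date, 2013-2016 | First visit, 2021-2024 | At first visit, 2021-2024 | All |
| Non-attenders, both arms | 2013-2016 | Completion of mailed questionnaires | By mail, apparently at the end | Apparently all |
| Deaths before the form is due | 2013-2016 | Death | Not completed | None |

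The entry for non-attenders is an inference. Section 1.5 speaks of mailed questionnaires without naming this one, and section 1.6.1.1 gives no mailing date for intervention non-attenders.

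**Step 2. Could attenders complete it again later?** The phrase about completing it before the clinic visit might mean every visit. Against that, section 1.6.1.1 twice refers to the first visit and schedules no repeat, while the protocol states end-of-follow-up measurement explicitly for other instruments. A single completion is the natural reading. If repeats were intended, the text has to say so.

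**Step 3. How many are affected?** Section 1.2.2 gives 450 invited, attendance of 60-70%, and around 300 attenders.
- 450 × 0.60 = 270; 450 × 0.65 = 292.5; 450 × 0.70 = 315. The stated figure is reproduced.
- Intervention non-attenders: 450 − 315 = 135 to 450 − 270 = 180.
- Controls answering at the stated 90-95% response: 450 × 0.90 = 405 to 450 × 0.95 = 427.5, before removing deaths.

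So 270-315 intervention survivors have essentially no self-report for a follow-up with an expected median of 8 years.

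**Step 4. Illustrative size.** Let *a* be attendance and *s* the proportion by which self-report raises captured events above those found by the common sources. The documents give no value for *s*; 5-15% is assumed. Take no true effect, full response, and no contribution from clinic records. Controls and intervention non-attenders then capture 1 + *s*, and attenders capture 1.

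Intention-to-screen ratio = [(1 − *a*)(1 + *s*) + *a*] / (1 + *s*). With *a* = 0.65:
- *s* = 0.05: (0.35 × 1.05 + 0.65) / 1.05 = 1.0175 / 1.05 = 0.97
- *s* = 0.15: (0.35 × 1.15 + 0.65) / 1.15 = 1.0525 / 1.15 = 0.92

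**Step 5. How far could this reach DALYs?** In the protocol's own model (section 1.7.1), breast cancer plus cardiovascular disease account for 1.12 of the 1.18 control DALYs (1.12 / 1.18 = 95%) and hypothyroidism for 0.01. Section 1.6.1.1 gives these conditions registry, cause-of-death or general practitioner sources in both arms, which limits the effect on DALYs.

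**The case against.** The strongest reply is that the questionnaire is a supplement. Section 1.6.1.1 approaches the general practitioners of all patients for cardiovascular disease not needing admission, hypertension, hypercholesterolemia and hypothyroidism. Cancers, cardiac interventions, admissions and causes of death come from registries for both arms. Section 2.2 takes direct health care consumption from patient files. This stands, and it limits the effect on major events, DALYs and costs.

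A reader might go further and infer that controls alone have an extra source, so that their events are inflated and the result favours BETER. The documents do not support that, for two reasons. Intervention non-attenders are also mailed the form. And data managers extract all visits and test results from BETER clinic records, a source that controls lack and that may detect mild or symptomless disease in attenders. That is a second arm-specific source, not a correction, and the net bias could go either way.

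A reader might also take 1/1.15 = 0.87 to 1/1.05 = 0.95 as the false ratio. That contrasts attenders with controls, whereas section 1.8.1 calls the intention-to-screen analysis the most valid approach. It rests on the same assumed 5-15%.

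Finally, section 1.1 already provides cohort data for describing non-responders, so that part of the remedy is largely available.

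None of this makes the form comparable between the arms. Section 1.6.1 still presents it as a source "for all included survivors, to allow valid comparison between the intervention and comparison groups", and section 1.6.2.3 still uses it to compare health care use.

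**Conclusion.** The point holds as a difference in ascertainment. As written, the BETER questionnaire covers almost none of the follow-up of about 270-315 intervention attenders and all of it for living controls who respond. It cannot support the between-arm use given to it in sections 1.6.1 (2b), 1.6.1.1 and 1.6.2.3.

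The conclusion rests on reading section 1.6.1.1 as a single completion at the first visit, which is the natural reading. The net direction and size of any bias are unknown. The 0.97-0.92 range is an illustration under an assumed 5-15% contribution from self-report, 65% attendance, full response and no offset from clinic records. It should not be read as an estimate, nor as evidence of a bias towards BETER.

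Severity is moderate: one of several sources for a primary outcome is affected, and a secondary outcome more directly. No sample-size figure changes.

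**What to change.** **Preferred.** Add the medical-history, medication, screening-history and care-use items of the BETER questionnaire to the end-of-follow-up questionnaires that intervention attenders already receive in 2021-2024 (sections 1.6.1.4 and 1.6.1.5). State in section 1.6.1.1 when each group completes them, including the mailing date for intervention non-attenders. Both arms then report on the same period at the same point. This has to be settled before those data are collected, because equivalent self-report cannot be recovered later. It does not remove the intervention-only clinic records.

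**Otherwise.** Remove the BETER questionnaire as a source for between-arm comparisons in sections 1.6.1 (2b), 1.6.1.1 and 1.6.2.3, and use only sources that cover both arms over the same dates.

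**Attenders versus non-attenders.** Base this comparison on cohort and registry data dated before the invitation.

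**Cost.** A slightly longer questionnaire for about 300 attenders, or a change of wording only. The second option gives up self-reported detail on care received elsewhere.

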##### 1.6.1.2. Assessment of Burden of Disease

In the proposed study, burden of disease from morbidity and mortality from CVD (including risk factors), breast cancer,

hypothyroidism and overwhelming post splenectomy infections due to functional asplenia is measured in 'disability adjusted life-years' (DALYs). One DALY can be thought of as one lost year of "healthy" life. DALYs for a disease or health condition are calculated as the sum of the 'years of life lost' (YLL) due to premature mortality and the 'years lost due to disability' (YLD) for people living with the health condition or its consequences:  $DALY = YLL + YLD$ . The YLL correspond to the number of deaths multiplied by the standard life expectancy at the age at which death occurs. To estimate YLD for a particular health condition in a particular time period, the number of cases in that period is multiplied by the average duration of the disease (in years) and a weight factor (disability weight) that reflects the severity of the disease on a scale from 0 (perfect health) to 1 (dead). Disability weights are extracted from literature (18–21).

#### 1.6.1.3. Assessment of Health care costs

In order to calculate the actual health care costs incurred in both groups during the study follow-up, i.e. between 2013-2016 and 2021-2024, the screening and treatment costs associated with breast cancer, CVD (including risk factors for CVD), hypothyroidism and functional asplenia will be assessed based on a combination of the available standard tariffs. See also 2.2. Cost analysis.

#### 1.6.1.4. Assessment of Health-related quality of life (HRQoL)

In all survivors HRQoL will be assessed at end of follow-up in 2021-2024 using the Short Form Health Survey, a 36-item, self-reported survey of patient health (SF-36), and the 5 dimension/5-level EuroQoL (EQ-5D-5L) questionnaire. The SF-36 assesses HRQoL in 4 physical domains (physical functioning, role limitations due to physical problems, bodily pain, general health) and 4 mental domains (social functioning, role limitations due to emotional problems, mental health and vitality) with points ranging from zero to an optimum score of 100 points (22). From these domains a physical and mental component score (PCS and MCS) can be derived. The EQ-5D-5L assesses health-related problems in five domains (mobility, self-care, activities of daily living, pain/discomfort and anxiety/depression) to produce a utility value ranging from 0 (death) to 1 (perfect health) (23). Survivors who have declined the invitation to visit a BETER clinic will also be asked to fill in this questionnaire. Survivors in the control group will be asked to fill in these questionnaires before their first BETER visit.

#### 1.6.1.5. Assessment of Health-related productivity losses

To measure and subsequently value indirect costs that arise outside the scope of the health care system, we will use the iMTA Productivity Cost Questionnaire (iPCQ) to assess health-related productivity losses (24). The iPCQ includes 3 modules measuring productivity losses of paid work due to absence from work, reduced productivity while at work and productivity losses related to unpaid work. This questionnaire will be administered at the end of follow-up in 2021-2024. Survivors who have declined the invitation to visit a BETER clinic will also be asked to fill in this questionnaire. Survivors in the control group will be asked to fill in this questionnaire before their first BETER visit.

#### 1.6.2.1. Assessment of Adherence to the BETER guidelines

Adherence to the BETER guidelines by patients and health care providers will be assessed during follow-up between 2013-2016 and 2021-2024. We will assess whether survivors have followed recommendations for referral to medical specialists or to their GP (for cardiovascular risk management). Both for survivors and BETER health care providers we will assess whether the screening frequency during follow-up is adhered to.

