##### RESEARCH QUESTION

Compared to usual care (absence of structured survivorship care), is survivorship care at the BETER clinics effective in 1) reducing morbidity and mortality from late effects of lymphoma treatment and associated costs; 2) increasing health-related quality of life and 3) reducing productivity losses?

What are the adherence rates to the BETER guidelines from patient and health care provider perspectives and what specific (parts of the) guidelines have lower adherence?

Which patient characteristics are associated with lower attendance rates to the BETER clinic?

Is knowledge about late adverse effects, risk perception of and distress about late effects associated with BETER clinic attendance and adherence to the screening guidelines?

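### The adherence window inherits a follow-up rule that contradicts itself for attenders with no visit in 2021-2024; read as ending at the last visit, it drops screens missed after drop-out and overstates adherence

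*Protocol*

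**What the plan says.** Adherence is a secondary outcome (1.6.2) and a stated research question: "What are the adherence rates to the BETER guidelines from patient and health care provider perspectives", followed by which parts of the guidelines do worse. The Objective section uses it to find where BETER care can improve.

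Section 1.6.2.1 ties the measure to follow-up: "Both for survivors and BETER health care providers we will assess whether the screening frequency during follow-up is adhered to". The same section describes that follow-up as running from 2013-2016 to 2021-2024.

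Section 1.5 defines follow-up. For the intervention group it starts in 2013-2016, "when they were first invited to attend the BETER clinic", "and ends in 2021-2024 at their most recent BETER visit". Other end rules exist only for deaths and for survivors who do not attend, for whom follow-up ("non-attenders in both the intervention and control groups) ends on completion of the mailed questionnaires") stops at a different event. The section's stated aim is "To facilitate follow-up of at least 5 years at the BETER clinics", and it adds: "Expected median follow-up time is 8 years".

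Section 1.6.1.1 takes the intervention group's screening data from the records of BETER visits.

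**The concern.** The end of an attender's window is set by an attended visit, and attendance is part of what adherence is meant to measure. A survivor who came on schedule for some years and then stopped has no rule of their own: they are not a non-attender, and they may be alive. Their most recent visit does not fall in 2021-2024, so the section 1.5 sentence cannot be satisfied in both halves.

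An analyst who follows the last-visit half closes the window at an attended screen. Gaps between two attended visits still count; permanent drop-out does not. A programme that loses many survivors could then report high adherence, and the part of the research question about lower-adherence components would be answered with unequal losses from components screened at different intervals.

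**Working it through.** **No figure to reproduce.** The protocol states no adherence rate, no denominator and no drop-out rate among attenders. The denominator used here (screens due) is an assumption, though a natural one for adherence to a screening frequency.

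**Inputs from the protocol.** Median follow-up is 8 years (1.5). TSH is annual (1.3.1.3). Breast screening is annual at ages 30-60 in eligible women (1.3.1.2). Cardiovascular risk factors are screened every 5 years (1.3.1.1).

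**Assumed inputs.** A share d of attenders stops permanently after year k, with d = 10-40% and k = 2 or 4. While engaged, a share a of due screens is done, with a = 100% or 80%.

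**One survivor, annual screen, 8 screens due after the first visit.** Attends on schedule to year k, then stops.
- Window closed at last visit: k/k = 100%.
- Window of 8 years: k = 2 gives 2/8 = 25%; k = 4 gives 4/8 = 50%.

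**Cohort, annual screen.**
- Screens done per attender: a × [(1 − d) × 8 + d × k].
- Due, last-visit window: (1 − d) × 8 + d × k. Adherence = a.
- Due, fixed window: 8. Adherence = a × [1 − d × (1 − k/8)].
- Overstatement = a × d × (1 − k/8).

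| a | d | k | Last-visit window | 8-year window | Gap (points) |
|---|---|---|---|---|---|
| 100% | 10% | 4 | 100% | 95% | 5 |
| 100% | 40% | 2 | 100% | 70% | 30 |
| 80% | 10% | 4 | 80% | 76% | 4 |
| 80% | 40% | 2 | 80% | 56% | 24 |

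With d = 0 the gap is zero. It is never negative.

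**Alternative drop-out model.** Take a constant yearly drop-out h and count the first visit, so 9 annual screens are due at years 0 to 8. Fixed-window adherence is the mean of (1 − h)^k over k = 0 to 8: 82%, 68%, 57% and 48% for h = 5%, 10%, 15% and 20%, against 100% to the last visit.

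**Annual against 5-yearly.** Each drop-out removes 8 − k = 6 or 4 annual screens from the window, but only one 5-yearly screen (the one due at year 5). In percentage points the order depends on the counting.
- First visit counted, h = 10%: annual gap 100 − 68 = 32 points; 5-yearly adherence is (1 + 0.9^5)/2 = (1 + 0.59)/2 = 80%, a gap of about 20 points.
- Only screens after the first visit counted, drop-out after year 2 or 4, a = 100%: annual gap d × 0.75 or d × 0.5; 5-yearly gap d, because the single later screen is lost.

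Components are therefore affected unequally. The annual ones lose more screens, but their rate is not always the more distorted.

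**Attenders who do return in 2021-2024.** Their window still closes at an attended visit, so annual screens due between that visit and 2024 can also be lost.

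**The case against.** The best reply is that the protocol already has a calendar window. Section 1.5 contains the words placing the end in 2021-2024, and section 1.6.2.1 repeats that range for adherence. Section 1.6.1.4 places end of follow-up there for all survivors, and sections 1.6.1.3 and 1.6.2.3 use the same span for costs and health care use. The last-visit reading also sits badly with the aim of at least 5 years: someone who attended once would have a window ending at that first visit. On the calendar reading the bias disappears.

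This part stands. A reader might infer that missed screens after drop-out are never counted and that adherence is overstated by construction. The documents do not support that; it is true of one reading only.

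The reply does not settle the text. Nothing says which half governs for an attender last seen in, say, 2018, and placing the last visit in 2021-2024 presumes the continued attendance that adherence should test.

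Two further objections also stand. The size rests wholly on assumed drop-out, and nine annual screens do not fit every survivor, since breast screening applies to a subgroup of women and becomes biennial at 60. Scoring every screen without a BETER record as missed would also be wrong: sections 1.6.2.1 to 1.6.2.3 expect some care and screening at the GP or another hospital.

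The scoring details may belong in an analysis plan that is not shown. The end-of-follow-up rule does not: the protocol states it and ties adherence to it.

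**Conclusion.** The point holds as a contradiction in a stated rule, with a one-directional risk. For attenders with no visit in 2021-2024, section 1.5 gives two incompatible ends of follow-up, and section 1.6.2.1 inherits them. Under the last-visit reading adherence can only be too high; under the calendar reading this bias is absent. The 4 to 30 points for an annual screen illustrate 10-40% drop-out after year 2 or 4 over 8 years and do not estimate what this study will show.

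Unequal effects across components follow from their different intervals. The claim that annual components are always the more distorted should be limited to the number of screens lost, or to rates that count the first visit with a constant yearly drop-out.

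Adherence is a secondary outcome, and this point concerns its window, not the primary DALY comparison. It should be corrected because adherence is meant to guide improvement of the programme.

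**What to change.** In section 1.6.2.1, define an adherence window that does not depend on attendance:

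- Run it from the first BETER visit to one fixed date in 2021-2024 for all attenders, for example the date of record abstraction.
- Censor only at death or when the guideline component no longer applies to that survivor.
- Count every screen due in the window, including those after the last visit. State whether the first visit is in the denominator.
- Score a due screen as missed only if it is absent from the BETER records and from the hospital, GP and questionnaire sources planned in sections 1.6.2.2 and 1.6.2.3.
- Report adherence per component.

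Section 1.5 should also say which half of its rule applies to an attender with no visit in 2021-2024.

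Cost: mostly wording, using sources already planned, with a little more cross-checking. Compared with the last-visit reading, reported adherence will be less favourable if attenders drop out.
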